#### Within trial primary analysis

The primary measure for the economic analysis will be the incremental cost effectiveness ratio (ICER). Accordingly, no statistical tests of differences in mean costs or outcomes will be conducted. The ICER will be estimated as the:

$$\frac{\text{Cost}_{\text{intervention}} - \text{Cost}_{\text{usual care}}}{\text{Utility}_{\text{intervention}} - \text{Utility}_{\text{usual care}}}$$

The estimates of incremental costs and outcomes from the regression will be bootstrapped to simulate 10,000 pairs of net cost and net outcomes of the intervention group for a cost effectiveness acceptability analysis, as recommended by NICE for health technology appraisals (National Institute for Clinical Excellence, 2013). These simulated data will be used to estimate the probability that service user/carer led training and care planning is cost effective compared to usual care.

This approach re-values effects or benefits in monetary terms. However, in the UK there is no universally agreed monetary value for the types of benefit measures used in cost effectiveness analyses. An approach used in health care is to ask the question: what is the maximum amount decision makers are willing to pay to gain one unit of benefit? The simulated net utility values were revalued using a range of maximum willingness to pay values from £1 to £30,000 to gain one unit of outcome, based on the range of willingness to pay values implied by NICE decisions (Rawlins et al, 2004).

The data for the cost effectiveness acceptability curve will be derived by first revaluing each of the 10,000 net outcome scores from the bootstrap simulation by a single WTPT. This is repeated for each WTPT. A net benefit statistic (NB) for each pair of simulated net costs and net outcomes for each WTPT can then be calculated as

$$NB = (O * WTPT) - C, \text{ where } O = \text{net outcome score and } C = \text{net cost.}$$

This calculation is repeated for each WTPT. Cost-effectiveness acceptability curves plot the proportion of bootstrapped simulations where the net benefit of an intervention is greater than zero for each WTPT (Fenwick et al, 2001; Sendi et al, 2001; Hoch et al, 2002; Briggs et al, 2001).

Assuming a 'cluster cohort' design is used factors known to influence costs and QALYs (e.g. ethnicity, socio economic status, previous service use) will be collected at baseline to statistically control for their impact (Davies 2007; 2008). A linear mixed model with a random effect for cluster will be used in all trial based analyses to control for these.

Descriptive analysis and data manipulation will be conducted using SPSS, and the main statistical analyses and estimation of net benefit statistics and cost-effectiveness acceptability analysis will be conducted using STATA.

## Within trial sensitivity analyses

Sensitivity analyses will explore whether the conclusions of the primary analysis will change in the following cases

Alternative assumptions about the duration and breadth of the effect of training are used to estimate the cost per participant of the intervention

The primary measures of outcome for the clinical evaluation are used as the measure of health benefit to estimate the ICER

The costs and QALYs are extrapolated to 12 months.

Case 1 will assume that the cost per day of health and social care estimated for the 3 month follow up is constant over the following 9 months and that the health status and utility value estimated at the 3 month follow up is constant over the following 9 months

Case 2 will assume that the cost per day of health and social care estimated for the 3 month follow up declines over the following 9 months and that the health status and utility value estimated at the 3 month follow up is constant over the following 9 months

Case 3 will assume that the cost per day of health and social care estimated for the 3 month follow up declines over the following 9 months and that the health status and utility value estimated at the 3 month follow up also declines over the following 9 months

Case 4 will assume that the cost per day of health and social care estimated for the 3 month follow up increases over the following 9 months and that the health status and utility value estimated at the 3 month follow up is constant over the following 9 months

Case 5 will assume that the cost per day of health and social care estimated for the 3 month follow up increases over the following 9 months and that the health status and utility value estimated at the 3 month follow up also increases over the following 9 months

Case 6 will assume that the cost per day of health and social care estimated for the 3 month follow up increases over the following 9 months and that the health status and utility value estimated at the 3 month follow up declines over the following 9 months

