Service users in the 'cluster cohort' will undertake a detailed face to face assessment at two points in time (baseline and 6 months). For these, we will adopt a formal written consent procedure. We will explain to service users that their community teams are involved in a study to test the effectiveness of a new training package on service user/carer involvement in care planning compared to the usual care planning experience. Participants will be told that we will do this by delivering the training to some mental health teams and not to other teams to see if receiving the training has an impact on the extent of service user/carer involvement in care planning.

Carers in the 'cluster cohort' will undertake a postal survey at baseline and at six months. Carers will be asked to participate via nomination by a service user. Response to the questionnaires will be treated as consent. Carers will also be asked to complete a baseline questionnaire and a consent to contact form in six months to allow the follow up questionnaire to be completed which is returnable to the research team in the prepaid envelope provided.

Service users in the 'cross sectional sample' will undertake a short postal survey at six months only. For these, we will treat this part of the study as a survey. Service users will receive a postal invitation to the survey, seeking their views on the quality of the care planning process that they have received. Response to the survey will be treated as consent, as is usual in survey work. Respondents will receive a £5 voucher for completing the survey. A follow up letter may be sent to encourage responses.

We have utilised these procedures in a previous, similar study conducted as part of another NIHR programme grant (RP-PG-0407-10136, ethical approval Salford and Trafford, 09/H1004/6 Amendment 3).

The study will be registered on a public database prior to recruitment of patients and will receive an appropriate ISRCTN.

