### *Allocation of outcome measures*

### Cohort Sample

#### Service Users:

- Demographic data will be collected at baseline.
- Primary Outcome – The HCCQ will be administered to the cluster cohort sample at baseline and at the six month follow-up.
- Secondary Outcome – the following seven measures will be administered at baseline and six months: VSSS-54, GASS, WEMWBS, DREEM, HADS, CALPAS-12, WHOQOL-BREF, along with the PROM.
- Economic Outcome – the EQ-5D-5L and the Service Use questionnaire will be administered at baseline and at the six month follow-up.

This information will be collected via a face to face method. As the 'cluster cohort' assessment is more burdensome, service users will receive a £10 voucher for their time after completion of the interview at six months.

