## Cross-section Sample

### Service Users:

- Demographic data will be collected at the six month time point.
- Primary Outcome – The HCCQ will be administered at the six month time point only.
- Secondary Outcome – PROM
- Economic Outcome - The EQ-5D-5L and the service use questionnaire will be administered at the six month time point only.

This information will be collected via a postal method. All respondents will receive a £5 high street voucher if they provide their name and postal address. Names and addresses will be requested on a separate from the questionnaire.

There will be no collection of carer information in the cross-sectional part of the study.

Table 1 shows the list of measures to be used, with which respondents, and at what time points.

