### *Economic analysis*

A cost effectiveness acceptability analysis will be conducted, from the perspectives of health and social care providers and service users, the key stakeholders in treatment decisions. The time horizon for the primary economic analysis will be at scheduled follow up (six months). Data on service use and health status (EQ-5D-5L) for the economic analysis will be collected for all participants at baseline and follow-up.

Data about the use of primary and community care based services will be collected by questionnaire completed by interview with the service users at the baseline and six month follow up assessments (cohort group). This is to ensure completeness of data collection and help to ensure that any questions or uncertainties about what should be reported can be addressed by the researcher completing the assessment. Data will also be collected from the cross-sectional group at the six month time point via the postal survey.

The service use questionnaire will ask for information about whether hospital inpatient and outpatients services have been used and if so, the name of the hospital, and this will be checked via records held by the case manager electronic record systems (with patient consent).

An economic patient questionnaire (service use questionnaire) to collect the service use information from service users will be adapted from those used in previous mental health evaluations. Service users will be asked for information about the number of care planning meetings they have attended. Data will also be collected from health records (with consent) about the resources (staff and facilities) used in the care planning process. The data from the service use questionnaire will be combined with the data in the health records to allow a detailed description of the service use and costs associated with care planning.

The time and expenses of service users, carers and staff involved in providing and receiving the training intervention will be documented along with details of facilities used. These data will be used to estimate the total cost of the training package. For the primary analysis, the cost of the training package will be allocated to trial participants by dividing the total cost by the number of participants randomised to the intervention group. This assumes that the investment in the training intervention lasts for six months (and has no impact after that time) and will only benefit the staff

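### All six 12-month extrapolation cases start from a 3-month follow-up that the trial does not have, so this economic sensitivity analysis cannot be run as written

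*Protocol*

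**What the plan says.** In the protocol, the section Within trial sensitivity analyses lists three departures from the primary economic analysis. The third is: "The costs and QALYs are extrapolated to 12 months". Six cases then define it. Case 1 assumes for costs that "the cost per day of health and social care estimated for the 3 month follow up is constant over the following 9 months" and for outcomes that "the health status and utility value estimated at the 3 month follow up is constant over the following 9 months". Cases 2 to 6 vary whether cost and utility stay constant, rise or fall, but every one keeps the same 3-month starting point and the same 9-month extension, for both quantities.

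The rest of the protocol describes a single quantitative follow-up, at six months:

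- **Economic analysis:** "The time horizon for the primary economic analysis will be at scheduled follow up (six months"). Primary and community care use is to be "completed by interview with the service users at the baseline and six month follow up assessments (cohort group").
- **Allocation of outcome measures, cohort service users:** "the EQ-5D-5L and the Service Use questionnaire will be administered at baseline and at the six month follow-up".
- **Allocation of outcome measures, cross-sectional service users:** "The EQ-5D-5L and the service use questionnaire will be administered at the six month time point only".
- **Service user/carer consent:** cohort members are assessed face to face "at two points in time (baseline and 6 months").
- **Table 1 and Timetable:** Table 1 has baseline and 6-month columns only, and the Timetable lists one cohort follow-up, at 6 months.

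**The concern.** The extrapolation needs two inputs per arm: a utility and a daily cost at the last observed point. The cases name a point at which neither sample is assessed. Someone following the text has to invent a rule for filling the gap, and would do so after seeing the data unless the text is corrected first.

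What is at stake is the set of pre-specified 12-month cases in the within-trial evaluation. They bear on a limitation that the protocol itself admits. The primary economic analysis assumes that the training investment lasts six months and has no impact afterwards, and the protocol says that this may over-estimate the training cost if the effect lasts longer.

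**Working it through.** **Inputs from the protocol**

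- Target horizon: 12 months (Within trial sensitivity analyses).
- Starting point and extension in every case: 3 months, then 9 months (same section).
- Observed follow-up: six months (Economic analysis, Allocation of outcome measures, Table 1, Timetable).
- QALY rule: mean of adjacent utilities multiplied by the time between them (Economic analysis).

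**Step 1. Reproduce the stated horizon.** 3 + 9 = 12 months. The text agrees with itself on the horizon; what is wrong is the starting point.

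**Step 2. Look for a 3-month assessment.** There is none for EQ-5D-5L or service use in either sample. The other three-month intervals in the protocol are management and work stream meetings. The 12-month contact under In-depth and network interviews is a qualitative Study 7 interview without economic measures.

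**Step 3. Horizon from the data that will exist.** 12 − 6 = 6 months remain to be extrapolated. Changing only the starting point gives 6 + 9 = 15 months, which contradicts the stated 12. Both numbers have to change together.

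**Step 4. Effect of the choice of repair on QALYs.** The protocol gives no expected utility difference, so g is an assumption: the between-arm utility gain at six months in the cohort, with no difference at baseline. After the starting point utility is held constant, as in Cases 1, 2 and 4. Time is in years.

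- 6 + 6 months: 0.5 × g/2 + 0.5 × g = 0.25g + 0.50g = 0.75g.
- Six-month value treated as a 3-month value, plus 9 months: 0.25 × g/2 + 0.75 × g = 0.125g + 0.75g = 0.875g.
- 3-month value interpolated linearly (g/2), plus 9 months: 0.25 × (g/2)/2 + 0.75 × g/2 = 0.0625g + 0.375g = 0.4375g.
- Six-month value plus 9 months: 0.25g + 0.75g = 1.00g, but over 15 months.

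| Assumed g | 6 + 6 (12 months) | Relabelled 3 + 9 (12 months) | Interpolated 3 + 9 (12 months) | 6 + 9 (15 months) |
|---|---|---|---|---|
| 0.04 | 0.0300 | 0.0350 | 0.0175 | 0.0400 |
| 0.05 | 0.0375 | 0.0438 | 0.0219 | 0.0500 |
| 0.10 | 0.0750 | 0.0875 | 0.0438 | 0.1000 |

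Relative to 6 + 6, the two other 12-month readings are 0.875/0.75 = 1.17 (17% higher) and 0.4375/0.75 = 0.58 (42% lower). Under these assumptions the ratios do not depend on g. If g is zero, all the readings agree on no gain.

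**Step 5. Costs.** A 9-month extension in place of 6 makes the projected period 9/6 = 1.5 times as long. The protocol gives no cost figures, so no incremental cost, ICER or net benefit can be computed.

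**The case against.** The strongest reply is that this is an evident carry-over which any analyst would repair correctly. The section states 12 months, the trial lasts six, and so six remain. The 15-month version would require someone to change one number, leave the other and overlook the stated horizon. Much of that stands: 15 months is an unlikely outcome. But the text still names a measurement that will not exist, nothing else in the protocol corrects it, and two other readings keep the 12-month horizon while giving different answers.

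A second reply is that a 3-month value could be reconstructed. Utility could be interpolated, and part of the cost might be recovered from the hospital and care-planning records that the protocol also uses. Interpolation does not give a value estimated at a follow-up, and it replaces the observed change between months 3 and 6 with a projection. The questionnaire-based primary and community care costs would have no separate 3-month estimate.

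A third reply concerns weight, and it stands. This is one of three listed within-trial sensitivity analyses, and the protocol separately plans an economic model to look at other time periods.

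A reader might infer more than the protocol supports:

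- **That the slip flatters the intervention.** It need not. Relabelling the six-month value raises the QALY gain, whereas interpolation lowers it.
- **That the gain is overstated by a third (1.00g against 0.75g).** That sets a 15-month total against a 12-month one. It is a difference in horizon, not a bias in a 12-month estimate.
- **That the cost-effectiveness conclusion would change.** No ICER effect has been shown, and changes in projected cost and benefit may offset each other.
- **That a 3-month assessment was meant and has been dropped.** No schedule, table or timetable entry points to one.

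**Conclusion.** The concern holds as an internal contradiction. All six 12-month cases rest on a follow-up that the trial does not have, so they cannot be run as written. The size and direction of any error depend on how the gap is filled. Against 0.75g for the reading that fits the design, the other two 12-month readings give 0.875g and about 0.44g.

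Those multipliers assume no baseline utility difference, the protocol's own QALY rule, and constant utility after the starting point. They do not carry over to Cases 3, 5 and 6, where utility rises or falls. They apply to the cohort, since the cross-sectional sample has no baseline utility.

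Severity is moderate. The fault is certain and disables the whole set of 12-month cases, but it is confined to this economic sensitivity analysis. The primary clinical analysis and the primary six-month economic analysis are not affected.

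**What to change.** In Cases 1 to 6, change the starting point from the 3-month to the six-month follow-up and the extension from the following 9 months to the following 6 months, for both cost and utility. Each phrase occurs twice per case, so 12 instances of each must change (6 × 2), and the two must change together so that observed plus extrapolated time is 6 + 6 = 12 months.

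This costs wording only: no new data, assessments or participants. It should be done before the outcome data are examined, so that the repair is not chosen with the results in view.

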## Economic model

An economic model will be developed to explore the impact of the intervention over alternative time periods, in different settings and populations. The model structure will be developed from a focussed review of the economics literature about care planning and training and refined/validated by discussion with EQUIP research team. Data to populate the model will be derived from the focussed review of the economics literature, review of national databases and datasets (e.g. Hospital Episode Statistics) and the trial. The primary and sensitivity will use incremental cost effectiveness and cost effectiveness acceptability approach outlined for the within trial evaluation. Probabilistic sensitivity analysis will be used to assess the level of uncertainty due to the data. Deterministic sensitivity analysis will be used to explore the impact of structural uncertainty.

## Study 7

We will examine the processes involved in the development and adoption of user/carer involved care planning drawing on Normalisation Process Theory (NPT, May, 2007). NPT (which comprises of four components: coherence (sense making work), cognitive participation (relational work) , collective action (operational work), reflexive monitoring (appraisal work) has been developed from empirical studies of the implementation of complex interventions in health care contexts and in relation to mental health contexts in particular. We will focus on: (a) implementation of user/carer involved care planning - the way this is developed and translated into practices (of mental health professionals, users, carers and others); (b) embedding - the manner in which care planning becomes, (or does not become), routinely incorporated in everyday work of service users and professionals;(c) integration - how care planning is sustained as part of the everyday lives of individuals at work and at home d) networking - how it generates access to new networks and resources.

Analysis of interview and observational data will be conducted with reference to principles of the constant comparative method (Charmaz, 1995) whereby analysis will

be carried out concurrently with data collection so that emerging issues can be explored iteratively. Anonymised verbatim transcripts of audio recordings will be imported into the software package Atlas.ti for data management. Analysis will draw upon the techniques of grounded theory approaches (Glaser and Strauss, 1967) including initial coding of text segments, followed by re-coding and memo writing to generate conceptual themes driven by the Normalisation Process Theory (NPT). The transcripts will be read by at least two researchers. Themes (based on the four constructs of NPT) will be compared within and across cases, paying particular attention to negative cases and possible reasons for differences. In addition to the thematic analysis, an exploration of narratives will be valuable for the longitudinal study of the impact of care planning on individual cases. Both thematic and narrative approaches have been prominent in previous qualitative studies focused on the day-to-day living with mental health conditions, and will serve as complementary analytic techniques (Coffey and Atkinson, 1996). Analysis of diary records and observational data will be complementary to the above and where appropriate will be used to illustrate relevant issues emerging from the interviews or observation records and may be used to help elicit interview data.

## **User engagement**

### ***Study 5 and 7***

Service users and carers have been involved with key aspects of the trial and process evaluation development, including helping to develop and deliver the user/carer led training in care planning, deciding on the secondary outcome measures to be used and development of the PROM.

## **Governance and Ethical issues**

The key ethical concerns for the programme include confidentiality, participant anonymity and informed consent to participate in research. The study includes both mental health service users and carers as participants and as such there are specific ethical issues to be considered. Research governance principles and ethical committee approvals bind all applicants and their institutions. We will ensure we adopt the highest standards of research conduct including involvement of service user representation in both the management and delivery of the research.

This studies will be conducted in compliance with the study protocol, GCP and both University and NHS regulatory and monitoring requirements. The work stream teams will meet every three months and the CI will be responsible for the overall leadership, management and outputs of the programme. The PI from each site will maintain a log of the key milestones to be achieved against the timetable. The work stream leads will be responsible for the day to day running and co-ordination of the studies and will be accountable to the PI. All research associates will be supervised by the work stream leads.

